### Type of participants

The sample will be composed of 75 patients with depression. Considering the heterogeneity of this population, the following inclusion criteria will be adopted: (1) diagnosed with major depression (single episode or recurrent episodes) as assessed by the MINI [55]; (2) pharmacological treatment for depression (use of antidepressants); (3) not engaged in regular exercise program (e.g., aerobic and/or strength training) for the 6 months prior to the commencement of experimental period; (4) absence of severe motor impairments, musculoskeletal injury, severe respiratory diseases, acute pulmonary embolism, unstable angina pectoris or severe heart failure, vascular brain disease, severe cardiopulmonary dysfunction, acute myocardial infarction or early phase of rehabilitation (critical aortic stenosis, severe hypertrophic and obstructive cardiomyopathy, untreated malignant arrhythmias, untreated severe hypertension, severe pulmonary hypertension), stroke or neurological disease, symptomatic cardiac malformations (e.g., septal defects, patent ductus arteriosus or valvular stenosis), atrioventricular block grade II or III, left bundle-branch block, or ventricular complex arrhythmias.

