Power calculations were performed using data published by Kerling et al. [88] (effect size 0.25), who showed that an aerobic exercise program can positively change depression scores as assessed by the MADRS scale. The obtained sample size was 21 patients per group (power 0.85, alfa error 0.05, correlation between repeated measures of 0.8). Assuming a drop-out ratio of approximately 30%, we will determine 25 patients per group as appropriate.

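### The drop-out allowance is miscalculated: 21 per group with about 30% drop-out needs 30 per group, and the planned 25 leaves 17 to 18 completers

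*Protocol article*

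**What the plan says.** The sample-size paragraph under Data analysis and power calculations uses an effect size taken from a published aerobic exercise trial ("effect size 0.25"), with "power 0.85, alfa error 0.05" and a "correlation between repeated measures of 0.8". It reports: "The obtained sample size was 21 patients per group". The next sentence makes the drop-out allowance: "Assuming a drop-out ratio of approximately 30%, we will determine 25 patients per group as appropriate".

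The total agrees with 25 in each of three groups. Type of participants says "The sample will be composed of 75 patients with depression", and the abstract also gives seventy-five. So 25 per group is the number the trial will use and not a misprint. The article gives no other drop-out rate and no other inflation rule.

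**The concern.** The step from 21 to 25 is meant to protect the required number of completers against a stated loss. An increase of 4 on 21 is about 19% (25/21 = 1.19), which is too small to absorb a 30% loss. If the assumption is right, the trial will end with fewer patients than its own calculation calls for on the primary outcome, the change in MADRS. The justification for enrolling 75 people would then not deliver what it says. According to Trial status, nobody had been included when the article was written, so the statement could still be corrected before data collection.

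**Working it through.** **Inputs, all from the protocol article.** Required number 21 per group; drop-out about 30%; planned number 25 per group; three groups (control, CAE, AEMC); total 75; MADRS measured twice (before and after); effect size 0.25; power 0.85; alpha 0.05; correlation 0.8.

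**1. Can the 25 be reproduced?**
- Standard rule, n/(1 − d): 21/(1 − 0.30) = 30 per group, 90 in total.
- Common shortcut, n × (1 + d): 21 × 1.30 = 27.3, rounded up to 28.
- Neither gives 25. A 20% add-on comes close (21 × 1.20 = 25.2), but the article says 30%.

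**2. What does 25 per group deliver at 30%?**
- 25 × 0.70 = 17.5, so 17 to 18 completers per group.
- In total 75 × 0.70 = 52.5, against 3 × 21 = 63.

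**3. What drop-out does 25 per group tolerate?**
- 1 − 21/25 = 0.16, about half the stated rate.

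**4. Does the word approximately help?** Read it as 25% to 35%, an assumed range.
- At 25%: 21/0.75 = 28 needed; 25 × 0.75 = 18.75 left.
- At 35%: 21/0.65 = 32.3, so 33 needed; 25 × 0.65 = 16.25 left.
- No value in this range supports 25.

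**5. What does this do to power?** The article names neither the effect-size type nor the test. I assume a group-by-time F-test with 3 groups and 2 measurements, so noncentrality λ = f² × N × 2/(1 − 0.8), with 2 and N − 3 degrees of freedom.

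| Reading of 0.25 | N = 21 in total | N = 63 (21 per group) | N = 51 (17 per group) | N = 54 (18 per group) |
|---|---|---|---|---|
| Cohen's f = 0.25 | λ = 13.1, power 0.854 | λ = 39.4, above 0.999 | λ = 31.9, 0.999 | λ = 33.8, above 0.999 |
| Cohen's d = 0.25 (f = 0.125) | λ = 3.3, 0.30 | λ = 9.8, 0.79 | λ = 8.0, 0.69 | λ = 8.4, 0.71 |

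Neither row gives 0.85 at 21 per group. In the first row 0.85 is reached at 21 patients in total, which suggests, but does not prove, that a total was labelled as a per-group number.

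If one nevertheless accepts that 21 per group gives 0.85, the implied λ at F(2, 60) is 11.49. Scaled in proportion to N, power is 0.757 at 51, 0.771 at 52.5 and 0.784 at 54.

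**The case against.** **Incomplete patients still enter the mixed model.** This is true, but MADRS is measured only before and after the intervention. A patient lost before the second assessment adds almost nothing to the comparison of change between groups. The analysis section also removes missing values in its first analysis.

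**Adherence in the pilot was 95%.** The Discussion reports this for exercise adherence in healthy elderly people. It is not retention of patients with depression, and the power paragraph still assumes about 30%.

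**A journal article condenses the full protocol.** This would excuse an omission. Here all three numbers are printed, in adjoining sentences, and they conflict.

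**The 21 may itself be unreliable, so the shortfall may not matter.** This stands in part. With 0.25 read as Cohen's f and a group-by-time test, 17 to 18 completers per group would still have power above 0.99. That limits what can be said about the consequence. It does not repair the drop-out step, which is wrong for any reading of the effect size, since the article itself sets 21 per group as the requirement.

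**What a reader might infer.** It is tempting to conclude that the trial is underpowered, or that power falls from 0.85 to 0.76–0.78. The document does not support either. The second figure holds only if 21 per group gives 0.85, and the stated inputs do not reproduce that under the readings tried.

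**Conclusion.** The inconsistency is certain and rests on the article's own figures: 30 per group are needed against 25 planned (90 against 75 in total), with 17 to 18 expected completers per group against 21 (about 52 against 63 overall), and a tolerable drop-out of 16% against about 30% assumed. These figures assume that 21 means completers per group and that drop-outs contribute essentially nothing to the pre-to-post comparison.

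The effect on power is open. For a group-by-time F-test with the stated inputs, power at 17 to 18 per group runs from about 0.69–0.71 (0.25 as Cohen's d) to above 0.99 (0.25 as Cohen's f). No single reduced value should be quoted as established. The conclusion is that the stated drop-out allowance is not met, and nothing stronger.

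**What to change.** Keep 75 patients and restate the drop-out sentence in one of two ways:

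- State that 25 per group preserves 21 completers per group provided drop-out does not exceed 16%.
- Keep about 30% drop-out, state that 17 to 18 completers per group are expected, and give the power recomputed at that number. Before doing so, name the effect-size type (Cohen's f or d) and the test to which the calculation refers, and confirm whether 21 is a per-group or a total number.

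Do not insert 0.76–0.78 as the new power, since it inherits the unverified premise that 21 per group gives 0.85.

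The cost is a sentence or two of text and a less favourable stated drop-out tolerance or completer count. No arm, endpoint or analysis changes.

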## Discussion

The present study has the objective to verify if patients with depression randomized into one of two physical exercise interventions (AEMC or CAE) combined with traditional drug treatment will present distinct improvements in depression symptoms (MADRS). In addition, different outcomes commonly altered by depression and with the potential to be reversed by physical exercise (e.g., cognitive function, hippocampal volume, brain-derived neurotrophic factor, sleep parameters, cardiovascular risk parameters, suicidal behavior, functionality, and treatment costs) will be evaluated.

From an operational standpoint, a pilot study involving 45 healthy elderly people was carried out in 2017, considering interventions with AEMC (two levels) and CAE (stationary cycling). Data from the pilot study are under analysis, but greater improvements with regards to cognitive and motor aspects were observed in the group undergoing exercises with greater motor complexity. In addition, training interventions produced very high exercise adherence (95%), which may be a differential, considering the difficulties in maintaining adherence during a traditional physical exercise program [89]. The main objective of this pilot study was to establish training routines and assessments and to provide logistical experiences between the parties involved (BHU, University, institutions involved in implementing training interventions and evaluations, and researchers) for the development of the proposal with patients with depression.

To our knowledge, this is the first study to test the effect of adding physical exercise to traditional treatment in patients with depression in a primary health care setting in Brazil. In addition, the use of aerobic exercises with insertion of activities with progressively higher motor complexity has not yet been tested in this population. Considering that exercises with high motor complexity may promote changes in cortical activation [90] and possibly increase the volume of associated encephalic structures (i.e., hippocampus) [27] in healthy individuals, assessing such adaptations in patients with depression is of great interest for clinical practice and public policies.

Finally, determining the impact of physical exercise programs on the treatment costs of patients with depression in Brazil may lead to new polices on how to treat them while decreasing the associated costs [2].

### Trial status

No participants have been included in the study. Data collection will start on April 2018 and is expected to be concluded on December 2018. This is version 2 of this study. Version 1 was submitted to FAPESP (Funding agency) on July 29, 2015. The changes in version 2 were the use of MINI as a screening toll for depression, MADRS as the primary outcome for depression, inclusion of MRI for brain structure assessment, the use of a questionnaire for suicidal ideation and behavior, sleep parameters, and sleep-related accelerometry data.

### Ethics and dissemination

This trial is approved by the ethics committee of the Hospital Israelita Albert Einstein and the Department of Health of the city of São Paulo (CAAE) number 64888017.3.0000.0086. Trial registration is RBR-9zgxzd. According to Brazilian legislation, individual data will be stored for 5 years, and patient identification will not be made publicly available. As approved by the ethics committee, patients in need for ancillary care will be referred to the Brazilian public emergency service. As provided by the financing notice, at the end of the study the Principal Investigator should produce a research report with a focus on its use in the management of the Brazilian Unified National Health System.

## Abbreviations

AEMC: Aerobic exercise with motor complexity
BDNF: Brain-derived neurotrophic factor
BHU: Basic Health Unit
BRIAN: Biological Rhythms Interview of Assessment in Neuropsychiatry score
C: Control
CAE: Continuous aerobic exercise
FS: Feeling Scale
MADRS: Montgomery-Åsberg Depression Scale
MDD: Major depressive disorder
MINI: Mini International Neuropsychiatric Interview
MoCA: Montreal Cognitive Assessment
MRI: Magnetic resonance imaging
RAVLT: Rey’s Auditory-Verbal Learning Test
RPE: Rating of perceived exertion
TUG: Timed Up and Go test
VO_2peak_: Peak oxygen uptake
